## NRG ONCOLOGY

RTOG 0126 (10/18/04)

### A PHASE III RANDOMIZED STUDY OF HIGH DOSE 3D-CRT/IMRT VERSUS STANDARD DOSE 3D-CRT/IMRT IN PATIENTS TREATED FOR LOCALIZED PROSTATE CANCER (9/18/03)

#### SCHEMA (9/18/03)

|          |                                  |          |                                                |
|----------|----------------------------------|----------|------------------------------------------------|
| S | Gleason Score/PSA  | R | Arm 1 (minimum PTV prescription) |
| T | 1. Gleason 2-6                   | A | 3D-CRT or IMRT: 70.2 Gy in 39 fractions        |
| R | and PSA $\geq 10$ but $< 20$     | N |                                                |
| A |                                  | D |                                                |
| T | 2. Gleason 7                     | O | Arm 2 (Minimum PTV prescription) |
| I | and PSA $< 15$                   | M | 3D-CRT or IMRT: 79.2 Gy in 44 fractions        |
| F |                                  | I |                                                |
| Y |                                  | Z |                                                |
|          | Radiation Modality | E |                                                |
|          | 1. 3D-CRT                        |          |                                                |
|          | 2. IMRT                          |          |                                                |

Treatment is prescribed as a minimum to the planning target volume (PTV) to be delivered at a rate of 1.8 Gy/daily fraction. The PTV includes with margin a clinical target volume that encompasses the prostate and *proximal* seminal vesicles (See section 6.0). A “cone-down” after 55.8 Gy to a planning target volume encompassing the prostate only will be optional for forward planned 3D-CRT. (9/18/03)

#### **Eligibility:** (See Section 3.0 for details) (9/18/03)

- Histologically confirmed prostate adenocarcinoma within 180 days of randomization
- Zubrod Performance Scale 0-1
- Prostatic biopsy tumor grading by the Gleason Score Classification
- One of the following combinations of factors:
  - Clinical stage T1b-T2b, Gleason score 2-6, and prostate-specific antigen  $\geq 10$  but  $< 20$
  - Clinical stage T1b-T2b, Gleason score 7, and prostate-specific antigen  $< 15$
- Clinically negative lymph nodes or histologically negative by nodal sampling or dissection
- No distant metastases (*M0*)
- No previous or concurrent invasive cancers, other than localized basal cell or squamous cell skin carcinoma, unless continually disease free for at least 5 years
- No prior pelvic irradiation, prostate brachytherapy, or bilateral orchiectomy
- No previous or concurrent cytotoxic chemotherapy for this cancer
- No previous hormonal treatment (*no finasteride or phytoestrogen preparation within 3 months prior to registration*)
- No radical surgery or cryosurgery for prostate cancer
- Pretreatment evaluations must be completed as specified in Section 4.1
- Patients must sign study-specific informed consent form prior to randomization.

**Required Sample Size: 1520**

Institution # \_\_\_\_\_

RTOG 0126 (10/18/04)

Case # \_\_\_\_\_

**ELIGIBILITY CHECKLIST** (9/18/03) (4/18/06)

(page 1 of 3)

- \_\_\_\_\_(Y) 1. Is there histologically confirmed prostate adenocarcinoma within the past 180 days?
- \_\_\_\_\_(2-7) 2. What is the combined Gleason Score Classification ?
- \_\_\_\_\_( < 20) 3. What is the PSA level?
- \_\_\_\_\_(NA/Y) 4. If PSA is >10 and Gleason score 7, was a bone scan done?
- \_\_\_\_\_(T1b-T2b) 5. What is the T stage?
- \_\_\_\_\_(N) 6. Is there evidence of nodal metastases?
- \_\_\_\_\_(N) 7. Is there evidence of distant metastases?
- \_\_\_\_\_(Y) 8. Is there the following combination of factors?
- Clinical stage T1b-T2b, Gleason score 2-6, and prostate-specific antigen  $\geq 10$  but  $< 20$
  - Clinical stage T1b-T2b, Gleason score 7 and prostate-specific antigen  $< 15$
- \_\_\_\_\_(0-1) 9. What is the Zubrod Performance Status?
- \_\_\_\_\_(N) 10. Has the patient had prior pelvic radiation, prostate brachytherapy, bilateral orchiectomy, or cytotoxic chemotherapy for prostate cancer?
- \_\_\_\_\_(N) 11. Has the patient had prior radical surgery or cryosurgery for prostate carcinoma?
- \_\_\_\_\_(N) 12. Any previous hormonal therapy?
- \_\_\_\_\_(Y) 13. If patient was receiving finasteride or the phytoestrogen preparation, "PC-SPES", has it been discontinued 90 days prior to randomization?
- \_\_\_\_\_(N) 14. Has the patient had previous or concurrent invasive cancer within the past 5 years, other than localized basal cell or squamous cell skin carcinoma?
- \_\_\_\_\_(Y) 15. Were pre-treatment evaluations completed per Section 4.1 of the protocol?
- \_\_\_\_\_(N) 16. Are there any major medical or psychiatric illness, which would prevent completion of treatment and/or interference with follow up?

Institution # \_\_\_\_\_

RTOG 0126 (10/18/04)

**ELIGIBILITY CHECKLIST (9/18/03)**

Case # \_\_\_\_\_

(page 2 of 3)

**The following questions will be asked at Study Registration:**

- \_\_\_\_\_ 1. Name of institutional person registering this case?
- \_\_\_\_\_ (Y) 2. Has the Eligibility Checklist (*above*) been completed?
- \_\_\_\_\_ (Y) 3. Is the patient eligible for this study?
- \_\_\_\_\_ 4. Date the study-specific Consent Form was signed? (*must be prior to study entry*)
- \_\_\_\_\_ 5. Patient's Initials (*Last, First*) [Initials only, effective 2/2002]
- \_\_\_\_\_ 6. Verifying Physician
- \_\_\_\_\_ 7. Patient's ID Number
- \_\_\_\_\_ 8. Date of Birth
- \_\_\_\_\_ 9. Ethnic Category (*Hispanic or Latino, Not Hispanic or Latino, Unknown*)
- \_\_\_\_\_ 10. Race
- \_\_\_\_\_ 11. Gender
- \_\_\_\_\_ 12. Patient's Country of Residence
- \_\_\_\_\_ 13. Zip Code (*U.S. Residents*)
- \_\_\_\_\_ 14. Patient's Insurance Status
- \_\_\_\_\_ 15. Will any component of the patient's care be given at a military or VA facility?
- \_\_\_\_\_ 16. Treatment Start Date
- \_\_\_\_\_ (N/Y) 17. Tissue/blood kept for cancer research?
- \_\_\_\_\_ (N/Y) 18. Tissue/blood kept for medical research?
- \_\_\_\_\_ (N/Y) 19. Allow contact for future research?
- \_\_\_\_\_ 20. Specify Gleason Score/PSA (*Gleason 2-6 and PSA  $\geq 10$  but  $< 20$  or Gleason 7 and PSA  $< 15$* )

**(Continued on the next page)**

Institution # \_\_\_\_\_

RTOG 0126 (10/18/04)

Case # \_\_\_\_\_

**ELIGIBILITY CHECKLIST (9/18/03)**

*(page 3 of 3)*

\_\_\_\_\_ 21. Specify Radiation Modality (*3D-CRT* or *IMRT*)

\_\_\_\_\_ 22. Treatment Assignment

The Eligibility Checklist must be completed in its entirety prior to calling RTOG. The completed, signed, and dated Checklist used at study entry must be retained in the patient's study file and will be evaluated during an institutional NCI/RTOG audit.

Completed by \_\_\_\_\_

Date \_\_\_\_\_

## **1.0 INTRODUCTION**

### **1.1 Safety Of Dose Escalation**

Three-dimensional conformal radiation therapy (3D-CRT) offers therapeutic advantages in the management of prostate cancer. Several series have demonstrated a reduction in normal tissue toxicity, both acute and late, with the use of 3D-CRT. RTOG 94-06 has demonstrated that higher cumulative doses of radiation can be delivered with lower risks of late effects compared to historical controls. Preliminary results at dose levels (*specified as a minimum tumor dose*) of 68.4 Gy and 73.8 Gy have been published. Acute toxicity was low, with 53–54% of patients treated to the prostate alone having either no toxicity or grade 1 toxicity. Sixty-two percent of patients treated to the prostate and seminal vesicles followed by a prostate boost had either no toxicity or grade 1 toxicity at either dose level. Few patients (0–3%) experienced a grade 3 acute bowel or bladder toxicity, and there were no grade 4 or 5 toxicities. Late toxicity, the primary endpoint on 94-06, has been very low in all patient groups. The majority (81–85%) had either no toxicity or mild (*grade 1*) late toxicity. A single late grade 3 bladder toxicity in a patient treated to 73.8 Gy was recorded. There were no grade 4 or 5 late effects in any patient. Compared to historical RTOG controls (*studies 75-06, 77-06*) at 68.4 Gy, no grade 3 or greater late effects were observed when nearly 15 were expected ( $p < 0.05$ ). At 73.8 Gy, there was a single grade 3 toxicity in a patient when nearly 25 were expected ( $p < 0.0005$ ). This data was updated with further follow up and included patients with stage T3 disease who had received the study dose to both the prostate and seminal vesicles. The favorable low toxicity results in the first analysis persisted. Patients treated to the next dose level, 79.2 Gy, were analyzed and reported in Spring 2001. With a median follow-up of 27.6 months, only 3 (1.8%) patients experienced grade 3 late toxicity, 2 cases of which were related to bladder (*cystitis with gross hematuria*) and 1 related to rectum (*proctitis with rectal bleeding*). There were no grade 4 or 5 late complications. The inability to demonstrate a maximally tolerated dose (*MTD*) at 1.8 Gy fractions prompted the RTOG to continue the study at 2.0 Gy fractions with study arms at 74 Gy and 78 Gy. As of May 2001, follow up on these levels is too short to analyze for toxicity.

Similar dose escalation trials at Fox Chase Cancer Center (FCCC) and Memorial Sloan-Kettering Cancer Center (MSKCC) have demonstrated the ability to administer high dose image-guided external beam radiation therapy with acceptable toxicity. Zelefsky reported toxicity on the dose escalation series from MSKCC. In that study, the planning target volume includes prostate and seminal vesicles for all patients. For patients treated to a dose of 81 Gy with 3D-CRT, a separate boost plan was initiated after 72 Gy, which blocked the anterior rectal wall in all fields. The dose inhomogeneity within the PTV varied from 4% to 7%. Dose-volume histograms were used to assure that no more than 30% of the rectal wall and/or 50% of bladder wall received a maximum dose of 75.6 Gy. With IMRT, the part of the PTV that overlaps with the rectum is limited to 88% of the prescribed dose, and the part that overlaps the bladder is limited to 98% of the prescription. This prescription method is in contrast to the RTOG experience in which only patients with stage T3 received the full study dose to the seminal vesicles. The majority of RTOG 94-06 patients either was not treated to seminal vesicles or had a treatment volume reduction after 55.8 Gy. Bladder and rectal doses were not constrained prospectively due to the lack of data available at the time of protocol development and the desire to use the 94-06 data to define these normal tissue tolerance parameters.

In the series from MSKCC, the five-year actuarial likelihood of developing grade 2 and 3 late GI toxicities was 11% and 0.75%. A prescribed dose exceeding 75.6 Gy, a history of diabetes mellitus, and presence of acute GI symptoms during treatment were all associated with a greater risk of grade  $\geq 2$  late GI toxicities. The five-year actuarial likelihood of the development of grade 2 and 3 late GU toxicities was 10 percent and 3 percent. As in GI toxicity, dose exceeding 75.6 Gy and presence of acute GU symptoms were independent predictors of grade  $\geq 2$  late GU toxicity. It was concluded that dose escalation above 75.6 Gy should utilize intensity modulated radiotherapy in order to avoid grade 2 or greater toxicity.

Lee and colleagues at FCCC described an increase in rectal bleeding in their dose escalation study. When doses to the central axis exceeded 76 Gy, the relative risk of rectal bleeding was 2.0. This prompted Schulteiss et al. to introduce a lateral rectal block on the last 10 Gy of the prostate boost fields. This additional block reduced the rate of grade 2-4 rectal complications. There was an increased rate of GI and GU toxicity in patients receiving adjuvant hormone therapy, a result also described by Michalski in the first analysis of 94-06.

### **1.2 Dose Response**

Retrospective data from single institution series and the Patterns of Care analysis have suggested that prostate cancer is a dose responsive neoplasm: the higher the dose of radiation administered to the tumor, the more likely it is to attain local tumor control. With the availability of 3D-CRT, it is felt that the higher radiation doses achievable using this modality will improve local tumor control in patients with localized adenocarcinoma of the prostate. Local control is a critical endpoint in the management of patients with prostate cancer. Fuks, et al. have demonstrated that local tumor progression serves as a nidus for the development of subsequent distant metastases and may ultimately compromise patient survival.

Higher doses of radiation have been known to increase cancer control in patients with adenocarcinoma of the prostate. Unfortunately, high doses without careful conformal treatment planning leads to higher complication rates. As described above, the RTOG and single institution studies have demonstrated that higher doses of radiation therapy can be safely administered using 3D-CRT. In the single institution prospective phase I/II dose escalation trials, investigators at FCCC and MSKCC have reported that the higher radiation doses are leading to an improved biochemical disease-free survival in patients with localized prostate cancer. Doses in excess of 75.6 Gy to the prostate improve freedom from biochemical recurrence and local disease progression. Radiation dose administered to the target volume was as important a prognostic factor in both of these series as was PSA, clinical stage, and Gleason score.

Recently, Pollack reported in a single-institution randomized trial that patients receiving 78 Gy to an ICRU reference point within the gland had a better (79%) biochemically disease-free survival (BNED) than patients receiving 70 Gy (69%),  $p=0.058$ . The patients with a presenting PSA > 10 had the most dramatic improvement in freedom from PSA failure with a 75% BNED at 78 Gy versus 48% BNED at 70Gy,  $p=0.011$ . The patients in this risk group demonstrated a reduction in the incidence of distant metastases (98% *metastasis free*) after receiving 78 Gy compared to patients receiving 70 Gy (87% *metastasis free*),  $p=0.054$ . This provides supportive evidence of Fuks' hypothesis that inadequate local therapy will allow local tumor to become a source of metastatic disease.

### **1.3 Trial Justification**

This trial is felt to be important to prove that the higher doses achievable with 3D-CRT are justified by an improvement in local tumor control, BNED (*or freedom from PSA failure*), and overall survival. Data from single-arm phase II dose escalation studies have suggested an improvement in tumor control with higher doses, but this strategy has not yet been adopted by the community of radiation oncologists. The preliminary results from the MD Anderson Phase III trial (*that included only 301 evaluable patients*) may not show a sustainable advantage to high dose 3D-CRT, and it may not have been large enough to identify a survival advantage to higher doses (*as is proposed in this trial*). Furthermore, patients treated in the 70 Gy arm were not treated with 3D CRT techniques, high-dose arm patients had only a portion of their treatment given with 3D CRT, and the 78 Gy dose was prescribed to the isocenter. This prescription may represent a minimum dose to the prostate and margin of 74 Gy (*assuming just 5% heterogeneity in the PTV*). Thus, the results of this trial may not have fully utilized the advantages to 3D CRT, particularly because there was not a difference in the post-radiotherapy biopsy rate between the two dose arms. The data from MSKCC suggests that microscopic disease persists until the prescribed minimum dose exceeds 75.6Gy.

A randomized study is being conducted at Massachusetts General Hospital and Loma Linda using proton beam to treat patients to doses of 70.2 Gy vs 79.2 Gy. The primary endpoint of this study is local control. Although this study is important, the applicability of the results from the trial will be restricted due to the limited availability of proton therapy in US radiation oncology facilities, and the relatively small sample size may not be able to test the hypothesis that higher dose results in improved local tumor control and this in turn improves survivorship.

The Medical Research Council (MRC) in the United Kingdom is also conducting a randomized trial of high dose versus low dose conformal radiation therapy. In this trial, the conventional dose is 64 Gy, and the experimental arm is 74Gy; both arms prescribing dose to the isocenter (*personal communication, [name]*). Due to the lack of PSA screening in the UK, patients in this study are likely to have more advanced cancer than those we anticipate registering to this trial. Furthermore, even the high dose arm is not strikingly higher than our low dose control arm, after correction for prescription point and target volume heterogeneity.

The Netherlands Cancer Institute (NKI) is conducting a randomized dose study using 3D-CRT in both arms. Like the MD Anderson and MRC trials, the dose prescription is to the isocenter with 68 Gy as the standard dose arm and 78 Gy for the experimental arm (*personal communication, [name]*). This study includes patients of all stages and risk factors of disease. The target accrual is 600 patients with four stratification groups.

### **1.4 Patient Selection**

The dose escalation series from FCCC and MSKCC suggest that dose escalation is either not advantageous or minimally beneficial in patients with favorable prostate cancer. Zelefsky described the favorable population as being without adverse prognostic factors ( $PSA \leq 10$ , Gleason score 2 to 6, clinical stage T1-2). Intermediate risk patients had a single adverse factor ( $PSA > 10$ , Gleason score  $\geq 7$ , or clinical stage  $> T2$ ), and unfavorable risk patients had two or more adverse risk factors. In the MSKCC series, the intermediate risk patients had the largest improvement in four-year BNED outcome with doses  $\geq 75.6$  Gy (79% versus 56%,  $p=0.04$ ). The unfavorable group also had a significant, but smaller, improvement (58% vs 30%,  $p=0.03$ ) in four-year BNED. Hanks reported a significant dose

response in patients presenting with PSA >10. Patients presenting with PSA >20 only had a significant improvement when receiving doses >75.6 Gy if they had no other adverse risk factors. This represented nearly 15% of their patients with initial PSA >20. Patients with PSA ≤10 demonstrated an improvement in BNED with higher doses if they had at least one adverse risk factor, including Gleason score ≥7, clinical stage T2b-T3, or perineural invasion.

The MD Anderson randomized trial benefited patients presenting with PSA >10. No other subset demonstrated as significant improvement in BNED outcome as did these patients.

In summary, the dose escalation and randomized series demonstrate the most striking dose effect in patients with “intermediate risk” prostate cancer. Patients with more favorable disease may not benefit from high doses because the volume of disease at diagnosis is small enough that conventional doses are adequate to eradicate disease. On the other hand, high-risk patients may have competing mortality from occult metastatic disease at diagnosis, and although they may have a local control benefit, long-term BNED and disease-free survival rates are unaffected. The patient population selected for this study corresponds closely to the patients in Group 2 on RTOG 94-06. The risk of seminal vesicle invasion exceeds 15%, but the risk of lymph node metastases is low. The treatment volume in these patients will be prostate and seminal vesicles treated to a dose that is expected to control microscopic disease followed by a boost to the prostate alone to the dose to which the patient was randomized.

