## 13.2 Sample Size

**13.2.1** *Stratification:* Patients will be stratified before randomization with respect to PSA and Gleason score: Gleason score 2-6 and PSA  $\geq 10$  but  $< 20$  vs. Gleason score 7 and PSA  $< 15$ , and Radiation Modality: 3D-CRT vs. IMRT. The treatment allocation scheme described by Zelen will be used because it balances patient factors other than institution. Patients will be randomized to MTD 3D-CRT or IMRT dose (79.2 Gy) vs. standard dose 3D-CRT or IMRT (70.2 Gy). (9/18/03)

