**13.4.4 *Analysis For Reporting the Initial Treatment Results: (9/18/03)*** This major analysis will occur after each patient has been potentially followed for a minimum of eight years for the primary endpoint, overall survival, and for a minimum of five years for the secondary endpoint, PSA failure, unless the early stopping rule is satisfied. It will include tabulation of all cases entered and those excluded from the analyses with the reasons for such given; the distribution of the important prognostic baseline variables; and observed results with respect to all the above mentioned endpoints. The primary hypothesis for the study is whether the higher total dose of 3D-CRT/IMRT will improve overall survival. All eligible patients randomized will be included in the comparison and will be grouped by assigned treatment in the analysis. The primary hypothesis of MTD 3D-CRT/IMRT treatment benefit will be tested using the Cox proportional hazard model with the major stratification factors included as fixed covariates. Additional analyses of treatment effect will include modifying factors such as age, race, and other patient characteristics. These analyses will also use the Cox proportional hazards model. The treatment comparison of time to PSA failure and disease-specific survival will be analyzed in a similar fashion. The treatment comparison of 2+ grade toxicity rates will use the z-statistic for testing binomial proportions. Also, where feasible, treatment comparisons with respect to time to PSA failure and overall survival will be compared within each ethnic category. Secondary analyses of the primary and secondary endpoints will be performed using the available Gleason scores from central review. Comparison of the proportion of patients with ED at one year by treatment arm will be performed using a chi-square test. Other comparisons will be made for subsets defined by the dose to the penis bulb and by age (<70 vs.  $\geq 70$  years old) respectively. Quality of life change scores from pretreatment to one year will be compared between treatment arms using a t-test. Quality of life will be correlated with responses on the IIEF. The z-test will be used to compare between treatment arms the average quality-adjusted survival within the first five years. An area under the curve analysis will be performed to compare the bowel and bladder symptoms assessed using FACE over the first five years.

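### The Section 13.4.4 Cox models for PSA failure and disease-specific survival adjust for disease risk only through a two-level Gleason/PSA stratum; adding entry PSA and T stage would be a cheap gain in precision

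*Protocol*

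**What the plan says.** - **Stratification (Section 13.2.1).** "Patients will be stratified before randomization with respect to PSA and Gleason score", in two levels: Gleason 2-6 with PSA at least 10 and below 20, and Gleason 7 with PSA below 15. Radiation modality is the second factor. T stage is not a factor.
- **Model (Section 13.4.4).** The primary hypothesis is tested in a Cox model with the stratification factors as fixed covariates. Then: "The treatment comparison of time to PSA failure and disease-specific survival will be analyzed in a similar fashion". Further models with age, race and other patient characteristics are described as additional.
- **Central review (Section 13.4.4).** "Secondary analyses of the primary and secondary endpoints will be performed using the available Gleason scores from central review". How the central score enters the model is not stated.
- **Prognosis (Section 1.2).** In two cited dose-escalation series, dose was "as important a prognostic factor in both of these series as was PSA, clinical stage, and Gleason score".
- **Risk grouping (Section 1.4).** Describing one of those series: "Intermediate risk patients had a single adverse factor" (PSA above 10, Gleason 7 or higher, or stage above T2), while "unfavorable risk patients had two or more adverse risk factors".
- **Eligibility.** The second admitted combination is "Clinical stage T1b-T2b, Gleason score 7, and prostate-specific antigen" below 15, with no lower PSA limit.

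**The concern.** Among eligible men the stratum level is fixed by Gleason score alone: every Gleason 2-6 man is in one level and every Gleason 7 man in the other. The PSA windows differ between the levels, so the stratum coefficient mixes a Gleason effect with an opposing PSA effect. Within the Gleason 7 level, men with PSA of 4 and of 14 are treated alike.

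Entry PSA and T stage are recorded for every man before randomization, and the protocol's own rationale calls them strong predictors. In a Cox model, omitting strong predictors pulls the treatment hazard ratio somewhat towards 1, leaves chance imbalance in those factors unadjusted and costs some power. At stake is the precision of two secondary efficacy comparisons. Their validity is not in question.

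**Working it through.** **Inputs.** From Sections 13.2.2 and 13.4.3.2: 1410 men accrued uniformly over five years; PSA-failure analysis at year 7; control hazard 0.074 per year; 2% per year dying without PSA failure; significance level 0.025, taken as one-sided (z = 1.96). From Section 13.2.2: 44% Gleason 2-6 and 56% Gleason 7, the mix in an earlier trial. From Section 1.4: four-year rates free of PSA failure of 79% v 56% (one factor, high v low dose) and 58% v 30% (two or more factors). The share of Gleason 7 men with PSA above 10 is not given; I assume 10% to 50%.

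**Step 1: reproduce Table 3.** I integrated the exponential model with competing deaths numerically.

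| HR | Failures: stated / computed | Power: stated / computed |
|---|---|---|
| 1.30 | 338 / 338 | 67% / 67.2% |
| 1.40 | 331 / 329 | 83% / 85.9% |
| 1.45 | 326 / 325 | 90% / 91.4% |
| 1.50 | 321 / 321 | 95% / 94.9% |
| 1.57 | 316 / 315 | 98% / 97.7% |

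Hand check at HR 1.30 with power = Φ(½√D × ln HR − 1.96): ½√338 = 9.19; 9.19 × 0.262 = 2.41; 2.41 − 1.96 = 0.45; Φ(0.45) = 67%. The model fits the table except for power at HR 1.40, where the stated figure is lower than its inputs give. That is separate from this point.

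**Step 2: risk ratio implied by the cited series.** With constant hazards, −ln(0.30)/4 = 0.301 and −ln(0.56)/4 = 0.145 per year at low dose, a ratio of 2.08. At high dose, ln(0.58)/ln(0.79) = 2.31.

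**Step 3: cost of pooling.** I used three prognostic groups (Gleason 2-6; Gleason 7 with one factor; Gleason 7 with two) and a control hazard averaging 0.074. A log-rank test stratified on the two planned levels was compared with one that also splits Gleason 7 at PSA 10. Ranges cover the assumed 10% to 50% share.

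| Risk ratio | HR | Planned strata | Split at PSA 10 | Loss (points) |
|---|---|---|---|---|
| 2.0 | 1.3 | 65.4-66.5% | 66.5-66.9% | 0.5-1.1 |
| 2.0 | 1.4 | 84.5-85.3% | 85.3-85.7% | 0.4-0.9 |
| 2.0 | 1.5 | 94.2-94.6% | 94.7-94.8% | 0.2-0.5 |
| 2.3 | 1.3 | 64.6-66.0% | 66.2-66.8% | 0.8-1.7 |
| 2.3 | 1.4 | 83.8-85.0% | 85.1-85.6% | 0.6-1.3 |

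The log hazard ratio is attenuated by 0.5% to 1.9%. Simulation (10,000 runs per setting) agrees. At HR 1.4, ratio 2 and a 30% share, power is 84.2% v 85.1%; at ratio 2.3 and a 50% share, 83.5% v 85.0%. One-sided type I error is 2.7% with the planned strata and 2.6% with the split, nominal within simulation error. A ratio of 3 would cost up to about 3 points at HR 1.3; at HR 1.4, power would still be about 82%.

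**Step 4: chance imbalance.** The Gleason 7 level holds about 0.56 × 1410 = 790 men. The SD of the between-arm difference in the two-factor share is √(4f(1−f)/790): 2.1 points at f = 0.1, 3.3 at 0.3 and 3.6 at 0.5.

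**Step 5: adding PSA and T stage more fully.** This needs an assumed further prognostic spread, for which the protocol gives no figure. Simulated Cox power at HR 1.4 (3000 runs per setting, 35% two-factor), composite v separate covariates:

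- Year 7, no extra spread: 82.8% v 84.1%.
- Year 7, SD of log hazard 0.3: 83.3% v 85.4%.
- Year 7, SD 0.5: 80.0% v 83.2%.
- Year 10, SD 0.5: 91.9% v 94.8%.

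Simulation error is not negligible here: composite power should fall, not rise, between the first two settings.

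**The case against.** Much of the case against stands.

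- **Whose definition.** A reader might infer that the protocol breaks its own definition of intermediate risk. It does not. Section 1.4 attributes the grouping to a cited series, describes the trial population as close to Group 2 of RTOG 94-06, and the eligibility criteria openly admit Gleason 7 with PSA below 15.
- **The two-fold ratio is borrowed.** The series' unfavorable group includes stage above T2, Gleason above 7 and PSA with no stated ceiling, all excluded here. Its low-dose one-factor hazard (0.145) is about twice this trial's planning rate (0.145/0.074 = 1.96). No rate is given for Gleason 7 with PSA of 10 to 15.
- **Uncontrolled risk.** A reader might infer bias. Randomization balances PSA and T stage in expectation, and type I error is nominal.
- **Which analysis.** A reader might attach the loss to the year-7 report. Section 13.4.3.2 names no adjusted Cox model for it, and Section 13.4.1 names Gray's test for PSA failure. The stratum-adjusted model belongs to the later analysis in Section 13.4.4, so the year-7 figures only indicate scale.
- **Central review.** A reader might infer that regraded men would be dropped. The planned levels have no place for Gleason 6 with PSA below 10, Gleason 7 with PSA of 15 to below 20, or Gleason 8 or higher. But the protocol never says that the composite will be rebuilt from central scores.
- **Dose benefit by risk group.** "The unfavorable group also had a significant, but smaller, improvement" depends on the scale. The gain is 58 − 30 = 28 points against 79 − 56 = 23, but as a hazard ratio it is smaller: ln(0.30)/ln(0.58) = 2.21 against ln(0.56)/ln(0.79) = 2.46. It is background text and drives no design quantity.

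The additional models in Section 13.4.4 do not dispose of the point. They are open-ended and supplementary, and do not bring PSA or T stage into the main comparison.

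**Conclusion.** The point holds as a modest improvement, not as the correction of an error. The main Cox comparisons of PSA failure and disease-specific survival leave out entry PSA (beyond the coarse stratum) and T stage, which the protocol itself ranks with dose.

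Pooling within the Gleason 7 level costs about 0.2 to 1.7 power points, given a two- to 2.3-fold risk and a 10% to 50% two-factor share. The ratio is probably an upper value, and the share is assumed. The promise of at least 80% power at a hazard ratio of 1.4 or more survives throughout that range. A gain of 2 to 3 points from fuller use of PSA and T stage is possible, but rests on an assumed SD of 0.3 to 0.5 in the log hazard.

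Power for disease-specific survival was not computed, nor was the cost of pooling alone at the later analysis time.

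**What to change.** In Section 13.4.4, for the Cox models of time to PSA failure and disease-specific survival, keep the stratification factors (including radiation modality) and prespecify log entry PSA and T stage as additional fixed covariates. With log PSA in the model, the stratum term becomes a Gleason contrast at equal PSA.

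For the central-review analyses, state that central Gleason enters as its own term, with a level for 8 or higher, alongside log PSA. Every reviewed man then has a defined place.

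The cost is analysis wording only: the data are already collected, and Table 3 projects over 300 PSA failures to support two more covariates. The downside is that the hazard ratio becomes conditional on more baseline factors, which the report should say.
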